
**Cannabis for the treatment of Chronic Headache**

Cannabis is a complex plant with many different active components. Clinical literature on the effectiveness of cannabis-based products for headache is summarized in Table 2. Cannabinoids can be administered in a variety of routes including inhalation, oral and sublingual routes or can be made with tea and mixed with edible items.[[25](#_heading=h.j8sehv), [52](#_heading=h.3dhjn8m)]. Cannabidiol (CBD) and Delta-9 Tetrahydrocannabinol (THC) are the two primary (and most abundant) active cannabinoids. [[53](#_heading=h.1smtxgf)] The direct mechanism by which cannabinoids work to modulate headache response is poorly understood. CBD acts as a negative allosteric modulator on the cannabinoid CB1 receptors and decreases the potencies of exogenous agonists (including THC) and 2-arachidonoyl-sn-glycerol (2-AG, an endocannabinoid).[[54](#_heading=h.4cmhg48)] CBD also potentiates anandamide mediated intrinsic neurotransmission.[[55](#_heading=h.2rrrqc1)]

**Table 2.** Clinical literature on Cannabis for the treatment of headache

| **Author** | **Year** | **Location** | **Study design** | **Population** | **Findings** |
| --- | --- | --- | --- | --- | --- |
| El- Mallakh  et al [[56](#_heading=h.16x20ju)] | 1987 | USA | Case series | Patient with a history of chronic smoking and migraine | Patients complain of headache after discontinuation of marijuana cigarettes; one patient got relief from headache after reinitiating cannabis smoking |
| Russo E et al. [[10](#_heading=h.3jtnz0s)] | 2001 | USA | Case series | Patient with a history of migraine | After the use of medical Cannabis, the patient experienced superior relief from headache as compared to ergots, opiates and beta-blockers |
| Grinspoon and Bakalar [[57](#_heading=h.3qwpj7n)] | 1997 | USA | Case report | Patient with a history of treatment failure for migraine | The patient got relieved from migraine with smoked Cannabis |
| Rhyne DN et al. [[58](#_heading=h.261ztfg)] | 2016 | 0USA | Retrospective, Observational chart review | Patients with migraine headaches on medical Cannabis therapy | Patients had a decrease in the headache episodes with the migraine therapy (10.4% to 4.6% monthly), reduction in frequency (19.8% decrease) and abortion of pain in 11.6% of the study participants |

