**Risk of Cannabis Dependence Screening**

During the design of this trial, the study team conducted focus groups with youth around medical cannabis adverse event reporting. Youth were asked to share their questions about medical cannabis products and shared concerns about the risk of dependence. Given their priority for this question, and the lack of data available to inform public health on the risk of cannabis dependence in youth when introducing them to high-CBD cannabis product, the Cannabis Use Disorder Identification Test Short-Form (CUDIT-SF) will be administered to trial participants at visit 1 and end-of-study visit.

CUDIT-SF is developed from the Cannabis Use Disorder Identification Test – Revised (CUDIT-R). [139] CUDIT-R was validated among college students and young adults (under 26 yrs). [136,137,138] Results indicate that CUDIT-R would validly distinguish between young adults with and without CUD and may be useful in screening for CUD in this high-risk population. [136,137] CUDIT-SF is a short form contains 3 questions from CUDIT-R (8 questions); study has demonstrated that the CUDIT-SF can quickly screen CUD in busy clinical setting while reducing the questionnaire administration burden on both clinicians and clinic patients. [139]

CUDIT-SF used in this trial contains the following questions:

Outside of the oil product that you are taking in this study, do you currently use cannabis? YES/NO

IF YES:

| 1. How often during the past 6 months did you find that you were not able to stop using cannabis once you had started? | | | | |
| --- | --- | --- | --- | --- |
| Never | Less than monthly | Monthly | Weekly | Daily or almost daily |
| 0 | 1 | 2 | 3 | 4 |
| 2. How often in the past 6 months have you devoted a great deal of your time to getting, using, or recovering from cannabis? | | | | |
| Never | Less than monthly | Monthly | Weekly | Daily or almost daily |
| 0 | 1 | 2 | 3 | 4 |
| 3. How often in the past 6 months have you had a problem with your memory or concentration after using cannabis? | | | | |
| Never | Less than monthly | Monthly | Weekly | Daily or almost daily |
| 0 | 1 | 2 | 3 | 4 |

The CUDIT-SF will not be used as an exclusion screening tool. If participant agrees not to use recreational cannabis during their trial participation, they should not be excluded from the trial.

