**Baseline Run-In Phase (from visit 1 to visit 2, the first month)**

Eligible adolescents will be asked by their healthcare providers if they are interested in learning more about this research study. A study team member, who is not involved in patients’ care, will present the study, consent documents and answer any questions from the patients and their families. Participants who meet the inclusion criteria and sign the informed consent (ICF) will be enrolled in the study.

Upon enrollment, baseline visit (visit 1) will be scheduled to collect participant’s demographic data, medical history and concomitant medicine history (in the past 2 years). In addition, an electronic headache diary will be set up for participant via REDCap.

C4T Baseline Safety Screening Tool for Cannabis-related interventional trials, also called SCR Checklist, will be used at visit 1 to capture thorough medical history, along with respective CTCAE grade level to document medical condition severity level at baseline. Medical conditions reported as medical history at baseline should not be reported as AE during the study, unless increases in frequency or severity. For instance: only fatigue increased in severity compared with baseline level should be reported as AE from baseline onwards.

Moreover, the baseline values (collected at visit 1) of each experimental measure will be estimated prior to administering the intervention/study product to the participants on visit 2. The participant will be asked to maintain the electronic headache diary, reporting headache-free days encountered by the participants, and will be asked to fill the following age validated scales (described above) on sleep related impairment, mood, and life impact. Participants will select three goals and work through goal attainment scaling each visit.

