## Exclusion Criteria

An individual who meets any of the following criteria will be excluded:

1. As per the investigator judgement, the participant is not an ideal candidate due to a personal issue or medical condition that is likely to impede in the successful completion of the study
2. Participants with a history of post-concussion headache or new daily persistent headache
3. Participants with a diagnosis of medication overuse headache
4. Participants with cardiac, renal or hepatic disease (assessed by the site investigator)
5. Participants with complex regional pain syndrome-II
6. Participants with abnormal ECG findings at baseline (as determined by the investigator)
7. Participants who are on the following medications: opioids, antipsychotics, antimanic, barbiturates, benzodiazepines, muscle relaxants, sedatives, or tramadol.
8. Participants with developmental delay or impairments including autism, cerebral palsy or intellectual disability.
9. Participants with a personal or family history of schizophrenia or psychotic disorders
10. Participants who are pregnant or breast/chest-feeding or plans to become pregnant within the study period or within three months of interventional product discontinuation
11. Participants who cannot commit to using contraception and refraining from recreational cannabis use and driving throughout the study period
12. Participants with known allergy to cannabinoids and/or palm/coconut oil

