## Lifestyle Considerations

Participants must agree to not drive during the study and the study visits. This is an absolute risk avoidance approach for the safety of participants and the public in the face of very little evidence supporting the safety of cannabidiol use while operating a motor vehicle. Participants will be asked to use contraception and will include monthly pregnancy tests. Female participants on hormonal contraceptives should be advised to use an additional alternative, non-hormonal/reliable barrier method of birth control during the study. Male, female and nonbinary participants will all be encouraged to continue contraceptive precautions for up to three months after discontinuation of cannabis-based therapies. Recreational cannabis use during the study will be discouraged.

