### Dosing and Administration

Eligible study participants will complete a baseline phase (first month) where no investigational product will be administered for one month. At the four subsequent study visits, study participants will receive escalating doses of CBD-enriched CHE from 0.2-0.4 mg/kg/day to 0.8-1 mg/kg/day for four months, with dose increases happening monthly over four months in 0.2mg increments. Participants will self-administer the investigational product orally following a dosing calendar and all dosing calculations will be based on weight at baseline. The product comes as CHE oil, 25% of the daily dose will be administered in the morning, and the remaining 75% of the dose in the afternoon to mimic endogenous cannabinoid diurnal variation. Upon completing the baseline phase, the eligible study participants will receive a supply of study products delivered to their home from the study central pharmacy at Children’s Hospital Research Institute of Manitoba (CHRIM). Each package will include a participant-specific dosing calendar for dose confirmation, and a return envelope to the central study pharmacy at CHRIM for used bottles to be mailed back for destruction and accountability.

During visit 2, study participants will be instructed how to administer the investigational product (IP) at a dose of 0.2-0.4 mg/kg/day divided into two doses (BID, 25% dose in morning and 75% in the afternoon) for one month. Participant’s day 1 of IP dose starts the day after visit 2.

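### Current cannabis users may enter on a promise to stop, so for them the pre-treatment headache diary is the first month off cannabis and may be a poor reference for the diary endpoints

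*Protocol*

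**What the plan says.** **Entry of users.** The protocol's section Risk of Cannabis Dependence Screening says "The CUDIT-SF will not be used as an exclusion screening tool" and then "If participant agrees not to use recreational cannabis during their trial participation, they should not be excluded from the trial". The questionnaire opens at visit 1 with "Outside of the oil product that you are taking in this study, do you currently use cannabis", so a yes at entry is foreseen. The only exclusion that concerns use looks forward: "Participants who cannot commit to using contraception and refraining from recreational cannabis use and driving throughout the study period". Lifestyle Considerations is softer: "Recreational cannabis use during the study will be discouraged". No section sets a limit on earlier use or a cannabis-free interval before visit 1.

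**The reference month.** Dosing and Administration says "Eligible study participants will complete a baseline phase (first month) where no investigational product will be administered for one month". For the same month the run-in text says "The participant will be asked to maintain the electronic headache diary, reporting headache-free days encountered by the participants". The daily pain rating also starts at visit 1.

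**How the month is used.** Objectives and Endpoints defines change from baseline in headache-free days and in average daily pain. The diary section reads a fall in intensity from baseline as efficacy. The study is open-label with one group, and the protocol's subgroups are sex and dose level.

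**The mechanism.** Table 2 of the Background summarises a case series: "Patients complain of headache after discontinuation of marijuana cigarettes; one patient got relief from headache after reinitiating cannabis smoking".

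**The concern.** A before-and-after comparison with no control arm depends on its before period. Someone who uses cannabis until entry and then keeps the promise to abstain spends the run-in in a changed state, not the usual one. If stopping brings on headache that later passes, the reference month has too few headache-free days and too much pain. The following months then improve without any drug effect.

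Dose rises in time order, visit by visit. Recovery over time would therefore also resemble a dose response, which is the relation that the first secondary objective sets out to study. Nothing in the protocol ties the data that would identify these participants to eligibility or to the reading of the diary endpoints.

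**Working it through.** **Figures in the plan that can be checked.** The sample size of 20 has no calculation behind it, so there is nothing to reproduce. The one related figure, the THC ceiling, does reproduce: 1.0 mg/kg/day CBD x 2/50 = 0.04 mg/kg/day. At the midpoint of the first dose step, THC is 0.3 x 2/50 = 0.012 mg/kg/day.

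**Timeline from the schedule of activities and the dosing section.**
- Visit 1, day 1: diary starts; the commitment to abstain applies from entry.
- Visit 2, day 30: pre-dose blood sample; dosing begins the next day.
- Visits 2 to 5: four monthly dose steps.

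The run-in text places baseline values at visit 1, but a monthly count of headache-free days cannot be taken on one day. The visit 1 to visit 2 diary is the only pre-treatment record from which it can come.

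**Shift in the group's run-in mean.** Let k be the number of users among 20 and w the headache-free days each loses in the run-in. The shift is (k/20) x w. The documents give neither k nor w, so both are assumed.
- k = 2, w = 3: 2/20 x 3 = 0.3 days a month.
- k = 6, w = 6: 6/20 x 6 = 1.8 days a month.

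Entry requires at least 15 headache days a month, so a 30-day month has at most 15 free days. The range is 0.3/15 = 2% to 1.8/15 = 12% of that maximum.

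**One mildly affected user.** Assume 10 true free days, 7 affected days and a quarter of the free days lost on those days. The user loses 10 x 0.25 x 7/30 = 0.58 days, and the group mean moves by 0.58/20 = 0.03 days.

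**Percentage change magnifies the effect.** For a user with 10 true free days, full recovery and no drug effect:
- 3 days lost: 10/7 - 1 = 43%. Averaged over 20 participants: 43/20 = about 2 percentage points.
- 6 days lost: 10/4 - 1 = 150%. Averaged over 20: 150/20 = 7.5 percentage points.

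**Pain intensity.** Assume a true mean rating of 5.
- One extra point for 7 days: baseline is 5 + 7/30 = 5.23, an apparent reduction of 0.23/5.23 = 4.5%.
- Two extra points for 21 days: baseline is 5 + 42/30 = 6.4, an apparent reduction of 1.4/6.4 = 21.9%.
- With 4 such users of 20, the group mean reduction is 0.9% to 4.4%.

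**Chance that the issue arises.** If 5%, 10% or 20% of eligible patients currently use cannabis (assumed), the chance of at least one among 20, 1 - (1 - p)^20, is 64%, 88% or 99%.

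**The case against.** The case against is substantial, and much of it stands.

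- **Adverse events.** A reader might infer that withdrawal symptoms would be counted as treatment-emergent at the lowest dose. The documents do not support this. Events are collected from consent, with onset dates and changes in severity, and start dates are reported. A symptom that begins on stopping at visit 1 is dated about a month before the first dose.
- **Other untreated time.** A reader might take the run-in as the only untreated headache record. It is not: Table 5 sets the last weaning week at 0 mg/kg/day while the diary continues. The run-in is the only pre-treatment record.
- **Duration and direction.** Calling the run-in a withdrawal month goes beyond the text. One case series shows that headache can follow stopping; it gives no duration or frequency and says nothing about occasional adolescent users. If cannabis had been relieving a participant's headache, the abstinent month could be the right untreated reference, with no bias.
- **Relief by the oil.** That the product itself relieves withdrawal is conjecture at THC doses of at most 0.04 mg/kg/day. The concern does not need it, because spontaneous recovery would be enough.
- **Questionnaires.** Their baselines are taken at visit 1, before the abstinent month, so this route does not inflate them.
- **Analysis plan.** Summaries with and without a subgroup are often left to the SAP, which is not shown, and individual listings would let a reader find users among 20 participants. The absence of such a summary is therefore not in itself a fault. Investigator judgement under the first exclusion may also keep out some heavy users.

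What remains is a protocol matter. The screening text directs sites not to exclude a user who promises to abstain, and a later analysis cannot replace a reference month already spent in an altered state.

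**Conclusion.** The point holds as a risk to the diary-based secondary endpoints, headache-free days and pain intensity, and no further. The protocol admits current users on a forward promise, starts the reference diary when abstinence begins, reads change from that month as improvement and has no control arm. Its own Table 2 gives a reason to expect headache after stopping.

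The size is unknown. The range of 0.3 to 1.8 headache-free days a month rests on assumed numbers of users and days lost, and on full recovery afterwards. With no users there is no effect, and with one mild user it is negligible. The primary adverse-event endpoint and the questionnaire baselines are not undermined by this route. It is a cheap improvement to a descriptive study, not a flaw in its main purpose.

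**What to change.** **Main change.** Define a recent-user flag before the data are examined. Base it on the current-use question at visit 1 and the plasma cannabinoids drawn before dosing at visits 1 and 2. Report change in headache-free days and in pain intensity for all participants and again without those flagged. Both sources are already collected. The questionnaire was added in version 6.0, so anyone who had visit 1 under an earlier version would be flagged from plasma alone.

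**Optional change.** The sponsor may define a cannabis-free interval before the baseline diary starts, and amend the screening text and the exclusion criterion on recreational use to match. The weaker wording in Lifestyle Considerations should be reconciled with that criterion in any case.

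**Cost.** The main change is one definition and one repeated summary, with 20 - k participants in the second version: 14 to 19 for 6 to 1 users. The optional change delays entry for some users. Neither alters the sample size or the primary analysis.

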## Schedule of Activities (SoA)

**Table 1.** CAN-CHA schedule of activities

| Study visit # | **1**  (Baseline) | **2** | **3** | **4** | **5** | **6** | **7** |
| --- | --- | --- | --- | --- | --- | --- | --- |
| Day # | **1** | **30** | **60** | **90** | **120** | **150** | **180** |
| Follow up window (days) | **±5** | **± 5** | **± 5** | **±5** | **± 5** | **±5** | **± 5** |
| Informed Consent | X |  |  |  |  |  |  |
| Demographics | X |  |  |  |  |  |  |
| Medical history (safety screening with SCR Checklist)^b^ | X |  |  |  |  |  |  |
| Review ongoing co-existing medical conditions^d^ |  | X | X | X | X | X | X |
| Concomitant medication and therapy review | X | X | X | X | X | X | X |
| IP intervention follow-up^a^ |  | X^a^ | X^a^ | X^a^ | X^a^ | X^a^ |  |
| Intervention dose of CBD (mg/kg/day) |  | 0.2- 0.4 | 0.4-0.6 | 0.6-0.8 | 0.8-1.0 | Wean |  |
| Physical exam | X |  |  |  |  |  | X |
| Vital signs and weight^c^ | X | X | X | X | X | X | X |
| Pregnancy test in females^e^ | X | X | X | X | X | X | X |
| Assign Daily eDiary via REDCap | X |  |  |  |  |  |  |
| Review of Daily Diary |  | X | X | X | X | X | X |
| Review of Adverse Events |  | X | X | X | X | X | X |
| Review of Cannabis-related Adverse Event |  | X | X | X | X | X | X |
| Cannabis Use Disorder Identification Test Short-Form (CUDIT-SF) | X |  |  |  |  |  | X |
| Pediatric Sleep-Related Impairment– Short Form 8a Scale | X | X | X | X | X | X | X |
| PedsQL Family Impact | X | X | X | X | X | X | X |
| Pediatric Short Form v2.0 - Anxiety - 8a scale | X | X | X | X | X | X | X |
| Pediatric Short Form v2.0 - Depressive Symptoms 8a scale | X | X | X | X | X | X | X |
| Pediatric Pain Interference – Short Form 8a scale | X | X | X | X | X | X | X |
| Pediatric Positive Affect – Short Form 8a | X | X | X | X | X | X | X |
| Self-directed goal attainment | X | X | X | X | X | X | X |
| Participant Trial Expectation Survey | X |  |  |  |  |  | X |
| Blood samples (8mLs, approx.) | X | X | X | X | X | X | X |
| Saliva Sample for Pharmacogenomics | X |  |  |  |  |  |  |
| Electrocardiogram (if not done in the last 3 months) | X |  |  |  |  |  |  |
| Drug Accountability |  | X | X | X | X | X | X |
| Visit duration (minutes) | 60 | 45 | 60 | 45 | 60 | 45 | 60 |

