Participant who scores 2 or higher will be considered a positive screen. Site study staff will notify the treating physician (site Qualified Investigator) when there is a positive screen (score above 2) and clinical care plans for managing potential cannabis use disorder will be followed.

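### The protocol gives two cut-offs for the cannabis use disorder screen, and a total of exactly 2 is positive under one and not under the other

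*Protocol*

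**What the plan says.** The Protocol, under Risk of Cannabis Dependence Screening, provides for the CUDIT-SF at visit 1 and at the end-of-study visit. A gate question comes first: "Outside of the oil product that you are taking in this study, do you currently use cannabis? YES/NO". Those who answer yes rate three items, each from 0 (never) to 4 (daily or almost daily).

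Two consecutive sentences then govern the result:

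- The definition: "Participant who scores 2 or higher will be considered a positive screen".
- The action: site staff notify the site Qualified Investigator "when there is a positive screen (score above 2". The bracket closes there, and the sentence goes on to require that care plans for possible cannabis use disorder be followed.

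The Schedule of Activities lists the "Cannabis Use Disorder Identification Test Short-Form (CUDIT-SF") at visits 1 and 7 without a cut-off. The Safety and Other Assessments section names cannabis use disorder screening among the assessments serving the primary safety objective, also without a cut-off. The Protocol Amendment History records only that version 6.0 added the form.

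**The concern.** The second sentence uses the term that the first has just defined, then attaches a different number to it. Staff who go by the defined term act on a total of 2. Staff who go by the number in the bracket do not. The bracket stands in the operative sentence, so it is a likely figure to be carried into a worksheet or a database alert.

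Two things are at stake. One is whether an adolescent with a total of 2 is brought to the treating physician's attention, which could differ across the three centres. The other is the reported count of positive screens, which would depend on the rule used.

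**Working it through.** **Inputs** (all from Risk of Cannabis Dependence Screening unless stated)

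- Three items, each an integer from 0 to 4, so the total T = i1 + i2 + i3 is an integer from 0 to 12.
- Rule A, the definition: positive if T ≥ 2.
- Rule B, the bracket in the action sentence: T > 2, which on an integer scale means T ≥ 3.
- 20 participants (Sample Size Determination) and two administrations each, at visits 1 and 7 (Schedule of Activities).

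**Where the rules differ.** For T = 0 or 1 both rules are negative. For T from 3 to 12 both are positive. For T = 2 Rule A is positive and Rule B is negative. T = 2 is the only value in conflict.

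**Which answers give T = 2.** There are 5 × 5 × 5 = 125 possible response patterns.

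| Total | Patterns |
|---|---|
| 0 | 1 |
| 1 | 3 |
| 2 | 6 |
| 3 to 12 | 125 − 10 = 115 |

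- Rule A: 125 − 1 − 3 = 121 positive patterns.
- Rule B: 125 − 1 − 3 − 6 = 115 positive patterns.
- Difference: 121 − 115 = 6. These are one item rated monthly (2) with the other two never (3 patterns), or two items rated less than monthly (1 each) with the third never (3 patterns).

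These are counts of answer patterns. They are not expected rates in patients.

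**How many forms could be affected.** The upper bound on forms is 20 × 2 = 40. Only those with a yes at the gate are scored, and of those only totals of exactly 2 are in conflict. The documents give neither the rate of cannabis use outside the trial nor any score distribution, so the expected number cannot be derived.

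**Whether another section settles it.** The three other places that mention the form or the screening (Schedule of Activities, Safety and Other Assessments, Protocol Amendment History) give no number. The only guide is the definition itself.

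**The case against.** The strongest reply is that the text largely resolves itself. The action is triggered by a positive screen, that term was defined one sentence earlier, and the bracket is a loose aside. That is fair as to intent, and it is why this is a wording correction. It does not remove the conflict, because the aside is a number in the sentence that staff act on, and it errs in the less protective direction.

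It can also be said that the score is not the only route to attention. Cannabis-related adverse events are reviewed at visits 2 to 7, drug misuse counts among adverse events, and development of dependency is given as an example of an event that may be serious. This stands, and it limits the consequence.

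A reader might infer a second contradiction: the gate asks about current use, while the items look back over six months ("How often during the past 6 months did you find that you were not able to stop using cannabis once you had started"). On that reading, recent users who have stopped are lost. The documents do not support calling this an error. The gate decides who is asked and the items set the recall period, so asking current users about the past six months is coherent. The commitment to abstain covers the time in the trial ("If participant agrees not to use recreational cannabis during their trial participation, they should not be excluded from the trial"; the Exclusion Criteria speak of "refraining from recreational cannabis use and driving throughout the study period"). The Baseline Run-In Phase text says "Upon enrollment, baseline visit (visit 1) will be scheduled", but the Schedule of Activities places consent at visit 1 itself, so a recent user may well still be a current user then.

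A six-month gate would bring its own difficulty. Visit 1 is day 1 ± 5 and visit 7 is day 180 ± 5, a gap of 179 days (169 to 189). Six months is about 365.25 / 2 = 182.6 days. The look-back at visit 7 would therefore begin nominally 182.6 − 179 = 3.6 days before visit 1, and up to 182.6 − 169 = 13.6 days before it. Someone who used until visit 1 and then abstained as promised could truthfully answer yes and be scored on pre-study use. Changing the gate mid-trial would also make earlier and later forms less comparable.

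**Conclusion.** The contradiction is real and confined to one score. At a total of exactly 2 the definition says positive and the bracketed trigger says not. This follows from the two sentences and the item scoring alone and needs no assumption about patients.

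The importance is minor. The score does not enter an endpoint, eligibility or the dose-limiting criteria, at most 40 forms arise from the planned 20 participants, and the number with a total of 2 is unknown. A reader might infer that the primary safety results are compromised because the screening is listed under the primary safety objective. The documents do not support this, since the primary endpoint is the frequency and type of treatment-emergent adverse events.

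Which cut-off the published instrument validates cannot be checked from the protocol. The preference for 2 or higher rests on its being the protocol's explicit definition and the safer of the two.

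**What to change.** In Risk of Cannabis Dependence Screening, change the bracket in the notification sentence to *(score of 2 or higher)*, so that the definition and the action use one cut-off. Check that site worksheets and any REDCap alert use the same number. Re-check any total of 2 already recorded, and notify the Qualified Investigator where this was not done.

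The cost is one phrase, carried in the next amendment through ethics review, and a look at no more than 40 forms. At most a few more adolescents would be brought to the physician's attention. The gate question and the six-month items can stay as they are.
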